##### Gait biomechanics

In order to assess the gait biomechanics, a 3D gait analysis is performed in the Movement Laboratory of the Niederrhein University of Applied Sciences using two force plates (Bertec, Columbus, OH, USA) with a sampling frequency of 1000 Hz, including a low-pass filter of 500 Hz, and a 10-camera motion analysis system (Qualisys, Göteborg, Sweden), which captures kinematic data at 340 Hz. The two force plates are integrated into a 10-m-long walkway and are later used to detect touch down and toe off events of the foot during gait. Prior to the gait analysis, the measurement system is calibrated according to the manufacturer’s specifications. Then, 26 retro-reflective markers according to the Istituti Ortopedici Rizzoli (IOR) lower body marker set are placed on bony reference points with double-sided tape to record the participants’ gait kinematics [36]. The IOR marker set for the lower body is chosen over other specific marker sets, such as the Oxford foot model and the modified Rizzoli foot model, because Qualisys recommends it and it is well-established in clinical settings. This study focuses on assessing general spatiotemporal gait parameters and the kinematics of major lower extremity joints relevant to activities of daily living and sports, rather than fine movements between the forefoot and rearfoot. The latter may be of interest when specific questions arise regarding ankle and foot joint movements. A static reference measurement is taken from each participant, which is later used for scaling purposes. Participants are then instructed to walk across the walkway at their self-selected walking speed and five valid right and left trials are recorded. Kinematic and kinetic data are processed using QTM Qualisys Track Manager—software, version 2022.2 (Qualisys, Göteborg, Sweden). Lower extremity joint angles, ground reaction forces, joint moments, and spatiotemporal gait parameters are presented in a gait analysis report based on a template by Baker et al. [37]. Relevant gait parameters are vertical, antero-posterior and mediolateral ground reaction forces (N), ankle, knee and hip angles (°), and cadence (steps/min), step length (m), stride length (m), stride width (m), and gait speed (ms−1). In addition, data are processed using the visual 3D software (©HAS-Motion, Canada). Instrumented gait analysis is considered reliable, with mean intraclass correlation coefficients (ICC) ranging from 0.95 to 0.97, mean standard error of measurement (SEM) values ranging from 2.01 to 2.47 degrees, and mean MDC values ranging from 5.86 to 7.02 degrees, and represents the gold standard for gait assessment in individuals with gait abnormalities [38, 39]. For all gait parameters, the difference in change between the groups is assessed and calculated using parametric statistical analysis. The method of aggregation is mean ± SD, and the measurements are taken before and after the 6-week intervention.

### Harms {17}

Adverse events, such as a recurrent ankle injury, other acute injuries, complaints, or illnesses, and any identifiable harm that the participant may experience as a result of the intervention, such as physical or psychological symptoms, are documented promptly. For this purpose, the investigator maintains regular contact with the participants. All adverse events will be reported in future publications. Participants are asked to report any significant deterioration of the ankle joint to the investigator immediately so that any necessary examinations can be initiated. Participant insurance is provided to all study participants. However, there is no provision for post-trial care.

### Participant timeline {18}

After a potential participant has contacted the study staff (AB) via email, the participant receives a self-administered questionnaire asking for basic socio-demographic and injury-related data and the CAIT to complete the initial eligibility screening. If the participant meets the eligibility criteria, an appointment is made for the first measurement in the laboratory. At the first appointment, all eligibility criteria are finalized and the participant is enrolled after providing informed consent. Outcome measures are then completed and the participant is assigned to one of the three groups by closed envelope. At the second appointment after the 6-week intervention, outcome measures are repeated. At the 4-week and 12-week follow-up visits, participants are contacted by email and asked to complete the FAAM questionnaire. A detailed description of the study procedure can be found in Table 6.

**Table 6 Tab6:** Study procedure

Time point	Investigation period				
	Entry	Baseline	According to the group categorization		
	<2 weeks	Time = 0 or preliminary examination and group classification	Intervention (6 weeks)	After the intervention	4 and 12 weeks after the intervention
Entry: Questionnaires	x				
Assignment		x			
Intervention					
Group 1: control			x		
Group 2: Mini Stability Trainer			x		
Group 3: Wobble Smart Board			x		
Assessments					
CAIT ^a^		x			
FAAM ^b^		x		x	x
YBT ^c^		x		x	
MBESS ^d^		x		x	
3D-Gait analysis		x		x	

^a^CAIT, Cumberland Ankle Instability Tool, ^b^
*FAAM *Foot and Ankle Ability Measure, ^c^*YBT *Y-Balance Test, ^d^*MBESS *Modified Balance Error System

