**Methods:**

This study is a prospective, single-center, interventional, randomized controlled trial with two comparison groups, either a usual balance training group or a control group. Individuals (18–44 years) with a self-reported ankle instability, a history of at least one ankle injury at least 12 months ago with typical signs of inflammation, two or more episodes of “giving way” within the previous 6 months, and a Cumberland Ankle Instability Tool score ≤ 24 are included. Exclusion criteria include acute injury, lower extremity surgery or fracture, neurological disease, chronic overuse injuries such as Achilles or patellar tendinopathy, and current participation in a targeted ankle rehabilitation program. The primary outcome measures are dynamic balance as measured by the Y-Balance Test and postural stability as assessed by the Modified Balance Error Scoring System. Secondary outcome measures include gait biomechanics measured by 3D gait analysis and self-reported ankle function assessed by the Foot and Ankle Ability Measure.

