### Ancillary and post-trial care {34}

Participants have the opportunity to liaise with physiotherapist AB via email during and after the program. Additionally, the program incorporates weekly meetings that can be conducted via Zoom.

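### Recurrent ankle injury is a named adverse event, but the 4- and 12-week contacts ask only for the FAAM, so re-injury may be under-counted and counted unequally by arm

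*Protocol article*

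**What the plan says.** Harms {17} lists what counts as an adverse event: "Adverse events, such as a recurrent ankle injury, other acute injuries, complaints, or illnesses", together with any identifiable harm from the intervention. These are to be recorded without delay, and all of them are to be published. Two routes are given. The first is investigator contact: "For this purpose, the investigator maintains regular contact with the participants". The second is self-report: "Participants are asked to report any significant deterioration of the ankle joint to the investigator immediately". Ancillary and post-trial care {34} adds that participants may reach the physiotherapist "via email during and after the program".

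Participant timeline {18} sets the schedule. For the post-intervention visit: "At the second appointment after the 6-week intervention, outcome measures are repeated". For what follows: "At the 4-week and 12-week follow-up visits, participants are contacted by email and asked to complete the FAAM questionnaire". In Table 6 the last column is headed "4 and 12 weeks after the intervention", and the FAAM is the only assessment marked in it. Table 6 has no adverse-event row for any period.

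**The concern.** The article promises prompt recording and full publication of re-injury, but the follow-up contacts it describes do not ask about it. The population makes the question relevant. Participants must report "two or more episodes of “giving way” within the previous 6 months" to enter, and they may continue sport, so further ankle injury during follow-up is plausible.

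Two things are at stake. The first is the harms report: if events come in mainly when someone volunteers them, the count may be too low, and it may be low to a different degree in each arm. The second is the interpretation of the FAAM, the only outcome collected after the 6-week visit. With 12 participants per arm, a low score at 12 weeks might reflect fading benefit, a new sprain or both. Without systematic information on new injury, a reader cannot reliably tell which.

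**Working it through.** The plan gives no figure for event-collection time, so there is nothing to reproduce. The check has three steps.

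**1. Share of observation after training.** Inputs are the 6-week intervention and the contacts 4 and 12 weeks after it (Participant timeline {18}, Table 6), and the target of 36 participants (Sample size {19}).

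- Contacts fall at weeks 6 + 4 = 10 and 6 + 12 = 18 from baseline.
- Share of time after training: 12 / (6 + 12) = 12/18 = 66.7%.
- In person-weeks, without dropout: 36 × 12 = 432 of 36 × 18 = 648.

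**2. Routes by which a re-injury could become known.**

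| Route | Section | Period | Who | Limits |
|---|---|---|---|---|
| Regular investigator contact | Harms {17} | No end stated | All | No frequency, no fixed question |
| Immediate self-report | Harms {17} | No end stated | All | Only marked worsening of the ankle, which is narrower than the adverse-event definition in the same section |
| Email access | Ancillary care {34} | During and after the program | All | On the participant's initiative |
| Weekly Zoom | Adherence {15c}, Ancillary care {34} | During the study; part of the program | Not limited by arm | For clearing up questions; no enquiry about events stated |
| Symptom notes in the booklet | Adherence {15c} | Training weeks | Two training arms | Symptoms during exercise |
| Being seen regularly | Oversight {3d} | Intervention only | Training arms, by its purpose | For adjusting the exercises |
| Follow-up emails | Participant timeline {18} | Weeks 10 and 18 | All | FAAM only |

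**3. What follows.** Only the two emails have a stated time after week 6, and neither carries an event question. The routes that remain open to everyone are unscheduled contact and self-report. The two routes that would bring out events during training, the booklet and the exercise visits, have no counterpart in the control arm. If ascertainment differs, recording is likely to be fuller in the training arms. That direction is an inference from the routes, not something the document states.

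**The case against.** A reader might infer that two thirds of the observation time has no event collection at all. The document does not support that. Neither route in Harms {17} stops at week 6, and the email channel in Ancillary care {34} stays open after the program. The 67% is the share of time in which event collection is unscheduled, not the share in which it is absent. Nor does Table 6 single out follow-up, since it has no adverse-event row for the training weeks either.

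A reader might also infer that the follow-up FAAM cannot be separated from new sprains. That is too strong as well. Sprains that are reported will be documented and can be set beside the scores. Re-injury may itself reflect lost or absent benefit of stability training, so function including its consequences is a legitimate comparison of the randomized groups. A sprain count helps explain that comparison; its validity does not depend on one.

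It is tempting to project the eligibility rate of giving way into a number of missed sprains and a shift in mean FAAM. The document gives no sprain rate and no FAAM loss per sprain, and giving way is not itself a named adverse event. The FAAM is summarized by medians and tested by rank methods, so comparing a shift in an arm mean with the minimum detectable change would be the wrong benchmark. No such size is claimed here.

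Finally, adverse-event forms and contact schedules often sit in a full protocol that an article condenses. That is fair, and their absence is not the point. The article does state what the 4- and 12-week contacts contain, and that content does not serve its own commitment on harms. Event data not solicited at these contacts cannot be restored at analysis.

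**Conclusion.** The point holds as a mismatch between the harms commitment and the follow-up schedule. For 12 of 18 weeks, ascertainment of re-injury rests on contact of unstated frequency and on self-report. During training the more active routes serve only the training arms. Under-counting and unequal counting by arm are therefore possible; how large they would be cannot be worked out from the document.

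The conclusion assumes that the follow-up emails contain what the article says they contain. If the full protocol already fixes an event question at these contacts for all three arms, the point falls away.

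Priority is low. The Y-Balance Test and the Modified Balance Error Scoring System are measured only before and after the 6 weeks, so the follow-up gap does not touch the primary outcomes. It bears on the harms report and on the reading of one secondary outcome.

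**What to change.** - Put the same short block of fixed questions to all three arms at the 6-week visit and in the existing 4- and 12-week emails: new ankle sprain (yes or no, date, side), other injury, and treatment received since the last contact. A count of giving-way episodes is optional.
- Add an adverse-event row to Table 6 that runs from the start of the intervention to the 12-week contact.
- Report re-sprains by arm, descriptively, beside the follow-up FAAM. Leave the planned intention-to-treat FAAM comparison unchanged.
- Ask participants already past their 12-week contact once, in retrospect, and flag those answers as recalled.

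The cost is a few extra questions in emails already being sent, a slight burden on participants, and a small amendment notified to the ethics committee and the registry, as Protocol amendments {31} provides. Because enrolment began in July 2023, some of the data will be recall-based.

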### Sample size {19}

An a priori sample size estimation based on the results of pilot measurements [40] examining change in dynamic balance after 6 weeks of balance training using the Mini Stability Trainer indicated that 33 participants (11 per group) would be needed to detect a mean difference of 4.6% in the composite score of the YBT with an effect size of *f* = 0.33 and a probability of 1 − *β* = 0.9 at a significance level of *α* = 0.05. To account for potential dropouts and loss to follow-up, the target number of participants is 36 (12 per group).

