### Explanation for the choice of comparator {9b}

The study comprises three comparison groups. The initial intervention is constituted by training with the Mini Stability Trainer. The Mini Stability Trainer facilitates targeted training of the forefoot and rearfoot. The targeted joints are of particular importance for the functional coupling of the forefoot and rearfoot. This is necessary to prevent possible consequences such as the development of osteoarthritis [15]. The second group is the standard treatment, which consists of balance training with a Wobble Smart Board. The primary objective of the study is to determine the comparative efficacy of the novel training intervention employing the Mini Stability Trainer in comparison to the conventional standard treatment. The second comparison is a control group without any training to assess if training with the Mini Stability Trainer is more effective than no training at all.

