### Outcomes {16}

#### Primary outcome measurements

##### Y-Balance Test

The Y-Balance Test (YBT) is a test of dynamic balance and is administered using a standardized test kit [25, 26]. In this study, the participant stands barefoot with the test leg on the stance platform of the test kit with the most distal portion of the big toe at the starting line. The hands are placed on the left and right iliac crest. The participant is instructed to move the target (reach indicator) with the free leg along the pipe as far as possible in the anterior, posteromedial, and posterolateral directions and to hold the end position for 3 s. Six trials are performed in each direction [27]. The first 3 trials are used to familiarize the participant with the task. The following 3 trials are recorded from the tape measure (5 mm increments) of each pipe at the edge of the reach indicator, at the point where the most distal point of the foot reaches, and used for further analysis. The participant is instructed to maintain balance during the trials and to return to the starting position after each trial. A trial is considered invalid and will be repeated if the participant touches the ground with the free leg, slips with the standing foot, falls off the stance platform, loses contact with the reach indicator while moving it to the maximum reach position, kicks the reach indicator forward, places the foot on the top of the reach indicator, or fails to return to the starting position under control. The maximum number of attempts is 3. The left leg is measured first. In addition, leg length is measured from the anterior superior iliac spine to the medial malleolus with the participant in the supine position to normalize anterior, posteromedial, and posterolateral reach distances to leg length. The following formula is used for normalization: reach distance/leg length × 100. The means of these normalized values are then calculated. In addition, the composite score is calculated using the following formula: (sum of the 3 reach distances)/3 times leg length × 100. In this study, the results are presented using the composite score. The minimum detectable change in YBT is between 7.7 and 14% [28]. The difference in change between the groups is assessed and calculated using parametric statistical analysis. The aggregation method is mean ± SD, and the measurements are taken before and after the 6-week intervention.

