## Statistical methods

### Statistical methods for primary and secondary outcomes {27a}

Primary and secondary outcome measures are reported descriptively using mean ± SD or median and interquartile range according to their type (e.g., ordinal or interval scale). After testing the data for normal distribution using the Shapiro-Wilk test and histograms, for the primary outcomes of dynamic balance (YBT) and postural stability (MBESS), the significance of differences in post-intervention change within and between groups will likely be analyzed using repeated measures analysis of variance (ANOVA) (YBT) or Friedman tests or Kruskal-Wallis tests (MBESS) and post hoc tests with Bonferroni correction to account for multiple testing. After testing the data for normal distribution using the Shapiro-Wilk test and histograms, for the secondary outcome of gait biomechanics, the significance of differences in post-intervention change within and between groups will likely be analyzed using repeated measures analysis of variance (ANOVA) and post hoc tests with Bonferroni correction to account for multiple testing. For the secondary outcome of joint function (FAAM), the significance of differences in post-intervention change within and between groups will be analyzed using Friedman tests or Kruskal-Wallis tests and post hoc tests with Bonferroni correction to account for multiple testing. The global significance level is set to *α* = 0.05. No additional analyses are planned.

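### The stated 90% power for a 4.6% YBT difference matches an overall three-group interaction test, not the Bonferroni-corrected pairwise comparisons that answer the trial's questions

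*Protocol article*

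**What the plan says.** Sample size {19} bases the calculation on pilot measurements "examining change in dynamic balance after 6 weeks of balance training using the Mini Stability Trainer". It concludes that "33 participants (11 per group) would be needed to detect a mean difference of 4.6% in the composite score of the YBT". The inputs it lists are f = 0.33, power 0.9 and α = 0.05. The target is then raised to 36 (12 per group) for dropout. The paragraph does not say which test or contrast carries the 90%.

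Statistical methods {27a} plans a repeated measures ANOVA for the YBT, followed by "post hoc tests with Bonferroni correction to account for multiple testing". The YBT is measured twice, before and after the six weeks.

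The questions are about pairs of arms. Explanation for the choice of comparator {9b} says: "The primary objective of the study is to determine the comparative efficacy of the novel training intervention", meaning the Mini Stability Trainer against standard wobble-board training. Objectives {10} hypothesises that both training arms improve similarly relative to control and do not differ from each other.

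The Y-Balance Test section adds a precision figure: "The minimum detectable change in YBT is between 7.7 and 14" per cent.

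**The concern.** A reader of item 19 will take it that the trial has 90% power for a 4.6% difference between groups. An overall F test over three arms does not say which arms differ, and its power is not the power of a corrected pairwise test. If the 90% belongs to the overall test, the comparisons on which conclusions will rest have less.

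This matters more than usual because one hypothesis predicts no difference between the two training arms. A non-significant pairwise result would then be read against a 90% figure that was not calculated for it.

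**Working it through.** **Inputs from the protocol:** N = 33 (11 per arm), f = 0.33, α = 0.05, power 0.9, difference 4.6%, k = 3 arms, m = 2 time points, MDC 7.7 to 14%. **Assumptions:** pre-post correlation ρ; three pairs as the Bonferroni family (α = 0.05/3 = 0.0167); two-sided tests with pooled error df of 3(n − 1).

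**1. Reproducing 33.** For the group-by-time interaction, λ = f²·N·m/(1 − ρ), with df 2 and N − 3. At ρ = 0.5 and N = 33, λ = 0.1089 × 33 × 2/0.5 = 14.37, giving power 0.907. N = 30 gives 0.874, so 33 is the smallest multiple of three that reaches 0.90.

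The result depends on ρ:

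| ρ | Power at N = 33 | N needed for 0.90 |
|---|---|---|
| 0 | 0.62 | 63 |
| 0.3 | 0.78 | 45 |
| 0.5 | 0.91 | 33 |
| 0.7 | 0.99 | 21 |

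Other tests that compare groups do not give 33. A one-way ANOVA with f = 0.33 has power 0.35 at N = 33 and needs 120. The between-groups main effect at ρ = 0.5 has power 0.45 and needs 93.

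**2. The SD this implies.** Take mean changes of 0, 4.6 and 4.6 (control, trainer, wobble board). Their mean is 3.07, and their SD (divisor 3) is 4.6 × √2/3 = 2.168. With two time points the interaction effects are half the deviations in change, so their SD is 1.084. Setting f = 0.33 gives an outcome SD of 1.084/0.33 = 3.29%. SD of change = SD × √(2(1 − ρ)), which at ρ = 0.5 is again 3.29%. As a check, N × (2/9) × 4.6²/3.29² returns λ of about 14.4.

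**3. Pairwise power on the same assumptions.** Noncentrality = 4.6/(3.29 × √(2/n)), which is 3.28 at n = 11 and 3.43 at n = 12. Training-versus-control power:

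- without correction: 0.89 (n = 11), 0.91 (n = 12);
- with Bonferroni: 0.77 (n = 11), 0.81 (n = 12).

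Reaching 0.90 with Bonferroni would take 15 per arm, 45 in total.

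**4. The protocol's own precision figure.** If the MDC is a 95% value for the composite score, the test-retest difference SD is MDC/1.96, that is 7.7/1.96 = 3.93 to 14/1.96 = 7.14. Both exceed 3.29.

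| SD of change | Overall power, N = 33 | Bonferroni pairwise, 11 per arm | Bonferroni pairwise, 12 per arm |
|---|---|---|---|
| 3.29 | 0.91 | 0.77 | 0.81 |
| 3.93 | 0.78 | 0.59 | 0.64 |
| 7.14 | 0.30 | 0.17 | 0.19 |

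**5. Detectable pairwise difference.** With 12 per arm, 90% power and α = 0.0167, the required noncentrality is about 3.845. The detectable difference is 3.845 × √(2/12) = 1.57 times the SD of change: 1.57 × 3.93 = 6.2% and 1.57 × 7.14 = 11.2%.

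**The case against.** **The calculation matches the planned model.** A repeated measures ANOVA is what {27a} plans for the YBT, and 33 is the required number for its interaction at ρ = 0.5. Sizing on an overall test and following it with post hoc pairs is common. This stands: there is no arithmetic error. A one-way reading, with its power of 0.35, tests a model that is not planned for the YBT and does not show one.

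**An article may leave the correlation and SD to a fuller document.** That also stands, and their absence alone is not the point. The point is that the published sentence attaches 90% to a mean difference of 4.6%, which the pairwise tests do not deliver on the assumptions that reproduce it.

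**Pairwise power could be higher.** Holding f at 0.33, Bonferroni power with 11 per arm is 0.95 at ρ = 0.7. But overall power at N = 33 would then be 0.99 and only 21 participants would be needed, which does not fit the stated 0.90 and 33. A linear pattern (0, 2.3, 4.6) gives 0.89 for the extreme pair with 11 per arm, but 0.28 for adjacent arms, and it is not the pattern hypothesised.

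**Stronger readings that the documents do not support:**

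- That 33 can come only from the interaction. The main effect of time at ρ = 0.4 also gives 33 (power 0.917), although it compares no groups.
- That no reported test has 90% power. The overall interaction does, on the assumptions in step 1.
- That power is certainly far too low. This rests on reading the MDC as a 95% value for the composite. The article gives neither the confidence level nor whether the range refers to the composite or to single reach directions.
- That 4.6% is a within-arm change. Item 19 speaks of change under one device, which suggests it. But the pilot is not shown, and the registration note says that this study was first designed as a randomised controlled pilot, so comparison arms cannot be excluded.

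**Trainer versus wobble board.** The protocol expects no difference here, so power to detect 4.6% is not the main issue. Inferring similarity from non-significance is a separate matter.

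**Conclusion.** The concern holds in a limited form. The 90% in item 19 is reproducible for the overall group-by-time interaction at a correlation of about 0.5. It does not carry over to the Bonferroni-corrected training-versus-control comparisons.

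In the best case consistent with the stated figures, the shortfall is moderate: 0.77 with 11 per arm, or 0.81 if all 12 per arm are measured. This rests on the hypothesised 0/4.6/4.6 pattern and a family of three pairs.

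The shortfall could be severe, and could reach the overall test as well, if the SD of change is what the protocol's own MDC suggests. That part is conditional on the MDC reading, and the documents cannot settle it.

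**What to change.** Keep 36 participants and restate item 19:

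- Name the test that carries the 0.90, with the pre-post correlation and SD of change it assumes.
- Check that SD against the MDC in the Y-Balance Test section. If a larger SD applies, restate the overall power too, and do not assert 0.90 for the interaction unconditionally.
- Say whether the pilot's 4.6% is a within-arm change or a difference between arms.
- Replace the implied 90% power for a 4.6% group difference with the Bonferroni pairwise power (about 0.81 at 12 per arm in the best case). Add the pairwise difference detectable with 90% power at 12 per arm (about 6.2% at an SD of 3.9% to 11.2% at 7.1%), and state the number of pairs in the family.

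The cost is one rewritten paragraph and a less favourable stated power. No extra participants are needed.

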### Objectives {10}

The study will be guided by the following specific objective: To determine whether the outcomes of dynamic balance, postural stability, gait biomechanics, and joint function improve in the intervention group and the balance training group after a 6-week intervention period and whether there is a significant difference compared to the control group.

The study is also based on the following hypotheses:The intervention group and the balance training group will lead to similar significant improvements in outcomes compared to the control group.It is also hypothesized that there will be no significant differences between the intervention group and the balance training group.

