### Trial design {12}

This study protocol follows the “Standard Protocol Items: Recommendations for Interventional Trials (SPIRIT) 2013 Statement” (https://www.equator-network.org/reporting-guidelines/spirit-2013-statement-defining-standard-protocol-items-for-clinical-trials/). The study is a prospective, single-center, interventional, randomized controlled trial with an intervention group (forefoot and rearfoot stability training) and two comparison groups, either a usual balance training group or a control group. It is a single-blind (principal investigator) design with patients randomized 1:1:1 to one of the three parallel groups. To ensure internal validity, a control group is included that does not receive any balance training intervention. Because many patients with CAI do not seek medical or physical therapy and continue with their usual activities, participants in the control group are allowed to do so. A summary of study information is presented in Table 1.

**Table 1 Tab1:** Study information

Category	Information
Country	Germany
Intervention	Active part: 6 weeks of training with the Mini Stability Trainer according to a predefined exercise schedule; 6 weeks of training with the Wobble Smart Board according to a predefined exercise schedule; one training session is performed under the supervision of a member of the study team, at least 17 training sessions are performed independently by each subject at home Control group: activities of daily living and sports activities; balance exercises are not allowed
Inclusion and exclusion criteria	Inclusion criteria: age between 18 and 44 years; based on the guidelines of the International Ankle Consortium: history of at least one ankle injury more than 1 year ago with typical signs of inflammation; self-reported ankle instability; in addition, two or more episodes of “giving way” must have occurred within the previous 6 months; Cumberland Ankle Instability Tool (CAIT ^a^) score ≤ 24 (in the case of bilateral ankle instability, the more severely affected side is selected) Exclusion criteria: acute injury, surgery or fracture of the lower extremity, neurological disorders, chronic overuse injuries such as Achilles or patellar tendinopathy; current participation in a targeted ankle rehabilitation program

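### The 90% power in the sample size section matches the omnibus group-by-time test; the Bonferroni-corrected contrasts that carry the first hypothesis have less, about 65% to 77% jointly if both training arms gain equally

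*Protocol article*

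**What the plan says.** Sample size {19} gives one calculation, based on pilot measurements of change in dynamic balance: "33 participants (11 per group) would be needed to detect a mean difference of 4.6% in the composite score of the YBT". Its inputs are f = 0.33, power 0.90 and α = 0.05. The target is then raised to 36 (12 per arm) to cover losses. The section names no test, no pre-post correlation and no division of α.

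The questions are about pairs of arms. Explanation for the choice of comparator {9b} states: "The primary objective of the study is to determine the comparative efficacy of the novel training intervention employing the Mini Stability Trainer" against standard balance training, with a second comparison against no training. Objectives {10} gives the first hypothesis: "The intervention group and the balance training group will lead to similar significant improvements in outcomes compared to the control group". The second hypothesis is that the two training arms do not differ.

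Statistical methods {27a} plans "repeated measures analysis of variance (ANOVA) (YBT) or Friedman tests or Kruskal-Wallis tests (MBESS) and post hoc tests with Bonferroni correction". It adds: "The global significance level is set to *α* = 0.05". It does not say how many comparisons the Bonferroni correction covers.

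**The concern.** A three-group interaction test that reaches significance shows that the arms do not all change alike. It does not show which arm differs from which. The first hypothesis is met only if each training arm is significantly better than control, and those two results come from the corrected post hoc tests. The sample size section nevertheless ties its 90% to detecting a mean difference, which reads as power for a comparison between two arms.

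At stake is how a non-significant contrast would be read. Set against a stated 10% risk of missing a real 4.6-point difference, a non-significant training-versus-control result looks fairly informative. If the corrected test misses such a difference about 15% to 23% of the time, and the two contrasts together fail about 23% to 35% of the time, the same result says much less.

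**Working it through.** **Inputs from the article.** f = 0.33, α = 0.05, power 0.90, N = 33 (11 per arm) or 36 (12 per arm), from Sample size {19}. Three arms, "patients randomized 1:1:1 to one of the three parallel groups", from Trial design {12}. Two Y-Balance Test occasions (before and after the 6 weeks), from Outcomes {16}. Repeated measures ANOVA with Bonferroni post hoc tests, from {27a}.

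**Assumptions, not in the article.** Pre-post correlation ρ = 0.5; the pattern of effects across arms; the number of contrasts corrected for (three pairs, or two contrasts against control).

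**Step 1: reproduce 33.** For the group-by-time interaction with m = 2 occasions, λ = f²·N·m/(1 − ρ) = 0.1089 × 33 × 2/0.5 = 14.37, on 2 and N − 3 = 30 degrees of freedom. Power is 0.874 at N = 30 and 0.907 at N = 33, so 33 is the smallest N that reaches 0.90. Other tests with the same f do not return 33: the time effect needs 27, the between-group effect 93 (equal arms), and a one-way ANOVA 120. If f is held and ρ is changed, the omnibus power at N = 33 becomes 78% (ρ = 0.3) or 99% (ρ = 0.7). The inference of ρ = 0.5 therefore rests on this exact match.

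**Step 2: translate f to a pairwise difference.** On change scores, f becomes 0.33 × √(2/0.5) = 0.66. If control gains 0 and both training arms gain d, the standard deviation of the three means is d·√2/3 = 0.4714d, so d = 0.66/0.4714 = 1.40 SD of change.

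**Step 3: power per contrast.** The non-centrality is d·√(n/2): 1.40 × √5.5 = 3.28 for n = 11 (30 df), and 1.40 × √6 = 3.43 for n = 12 (33 df), with pooled error and two-sided tests. Joint power is from simulation (400,000 runs) with the shared control arm.

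| Correction | Each contrast, 11 / 12 per arm | Both contrasts, 11 / 12 per arm |
|---|---|---|
| Three pairs (α = 0.05/3 = 0.0167) | 77% / 81% | 65% / 71% |
| Two contrasts (α = 0.025) | 82% / 85% | 72% / 77% |
| None (α = 0.05) | 89% / 91% | 82% / 86% |

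Pooled error is the favourable choice. Separate two-sample tests with 11 per arm and three pairs give 74% per contrast and 61% jointly. The figures for 12 per arm require that nobody is lost.

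**Step 4: another pattern.** If effects are evenly spaced (0, d/2, d), the standard deviation of the means is d/√6, so d = 0.66 × √6 = 1.617. The largest contrast then has non-centrality 1.617 × √5.5 = 3.79, and its power with three-pair Bonferroni is 89% (11 per arm) or 92% (12 per arm).

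**The case against.** The calculation is right for the analysis that the article names first. Repeated measures ANOVA is the planned Y-Balance Test analysis, the pairwise tests are called post hoc, and sizing on the omnibus test is common. Nowhere does the article claim 90% for each pair. This stands to the extent that nothing was miscalculated. It does not remove the mismatch, because the sentence attaches the power to a mean difference and the first hypothesis cannot be settled by the omnibus test.

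The pairwise figures also rest on a reconstruction. The correlation is inferred, the size of the Bonferroni family is not given, and the article does not say which contrast the 4.6% describes. This stands too, and it is why ranges are given. The equal-gain pattern, however, is the article's own first hypothesis.

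A reader might infer more: that the 90% is false for every pairwise difference the trial could declare. The documents do not support that. Under evenly spaced effects the largest contrast, if that is the 4.6-point one, has 89% to 92%, which is essentially the stated power. Nor is low power for a smaller difference between the two devices a fault of this sentence. The sample size section does not claim to detect one, and the second hypothesis predicts no difference, which power for a difference test does not address.

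**Conclusion.** The point holds as a misattributed power statement, not as an arithmetic error. N = 33 with 90% power is correct for the omnibus group-by-time test at f = 0.33 and ρ = 0.5. It is not the power of the corrected contrasts on which the first hypothesis depends.

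Accepting f = 0.33 and equal gains in both training arms, a single contrast has about 77% to 85% power, depending on whether three or two contrasts are corrected for and whether 11 or 12 per arm are evaluable. Both contrasts together have 65% to 77%. The joint figure stays below 90% even without correction (82% to 86%), so for the first hypothesis the conclusion does not depend on the Bonferroni count. The direction is firm under the equal-gain pattern; the exact percentages depend on the inferred correlation and on that pattern.

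**What to change.** Restate the sample size section so that it:

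- says that the 90% refers to the omnibus group-by-time test;
- names the correlation used;
- says which contrast the 4.6% describes;
- reports the power of the Bonferroni-corrected training-versus-control contrasts, singly and jointly, with the effect pattern and number of contrasts assumed.

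The authors should compute these figures from their own inputs. Under equal gains and ρ = 0.5 they should find about 77% to 85% per contrast and 65% to 77% for both.

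This is a change of wording with no change in enrolment. The cost is that the stated power becomes less favourable.
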